### Minimum sample size estimation

The minimum estimated sample size is 40 patients according to previous data, considering a prevalence of 60% of inadequate PUFA intake [55]. The following parameters were considered: baseline IFNγ = 3,986 ± 738 pg/mL, IFNγ after *n*-3 PUFA supplementation = 2,922 ± 1,275 pg/mL [56], power = 0.8, and α = 5%. We used the R project software with package 'Epicalc’ version 1.02 [57] to obtain this estimate.

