### Randomization and concealment

After the screening phase, patients will be randomly assigned to 1 of 2 groups of 20 patients each: intervention group or control group. Assignment to either group will be performed by a computer-generated 1:1 randomization. This assignment will occur within randomly ordered blocks of size 4 or 6. This procedure will be conducted using R project software with package 'blockrand’ [52].

The allocation sequence will be concealed from the researchers, who will enroll and assess participants in sequentially numbered, opaque, sealed, stapled envelopes. To prevent subversion of the allocation sequence, the name and date of birth of the participant will be written on the envelope before the envelope is opened. The information in the envelope will be transferred onto the allocation card inside the envelope. Corresponding envelopes will be opened only after the enrolled participants have completed all baseline assessments and at the time of allocation to the intervention. These procedures will be carried out by a professional without access to the baseline evaluation results. The blister packaging and gel capsules of omega-3 PUFAs and placebo will be identical. They will be identified by the lot number on the package, which will be retained in the pharmacy, and only the blisters will be provided to patients. The pharmacist responsible for distribution and compliance assessment will be the only person who can access this information.

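### The minimum of 40 patients at power 0.8 is not reproduced by the stated IFNγ inputs, which require 32 to 34 two-sided, and the role of the 60% prevalence is not stated

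*Protocol article*

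**What the plan says.** The section Minimum sample size estimation opens with "The minimum estimated sample size is 40 patients according to previous data, considering a prevalence of 60% of inadequate PUFA intake". It then lists its parameters: "baseline IFNγ = 3,986 ± 738 pg/mL", and for the value after n-3 PUFA "supplementation = 2,922 ± 1,275 pg/mL [56], power = 0.8, and α = 5" (per cent). It names an R package as the software. It does not give the sidedness of α, an allowance for losses, or the way the 60% enters the calculation.

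Randomization and concealment is consistent with the total: patients go to "1 of 2 groups of 20 patients each". Statistical methods plans a Student t test between the two groups, or a Wilcoxon test if the data are not normal, with P below 0.05 counted as significant in every test. Procedures, follow-up, and data collection allows patients to be excluded during follow-up for complications such as hospital admission or use of anti-inflammatory drugs.

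**The concern.** The section gives two means, two SDs, α, power and a result, so a reader can repeat the calculation. Repeating it for the planned test does not give 40. The text also attributes the 40 partly to a prevalence of inadequate PUFA intake, a quantity that a comparison of two means does not use. Intake is not an eligibility criterion either, so the 60% does not describe how the randomised population is selected.

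This paragraph is the only justification given for the trial's size. If its basis is unclear, so is the power of the trial. A reader faced with a null result needs to know whether 20 per arm was comfortable for the assumed effect or whether the authors expected only part of the sample to show it. An article may leave detail to a full protocol, but here the inputs and the result are both printed and do not agree.

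**Working it through.** **Inputs** (Minimum sample size estimation, except the arm size)
- Means 3,986 and 2,922 pg/mL: difference 1,064.
- SDs 738 and 1,275: 738² + 1,275² = 544,644 + 1,625,625 = 2,170,269.
- Power 0.8, α 5%. Two-sided is assumed because sidedness is not stated; one-sided is also tried.
- 20 per arm, 1:1 (Randomization and concealment).

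**Attempt to reproduce 40**

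n per arm = (z_α + z_power)² × (SD₁² + SD₂²) / difference²

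Two-sided: (1.960 + 0.842)² × 2,170,269 / 1,064² = 15.05, so 16 per arm, **32 in total**.

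The t distribution requires slightly more:

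| Per arm | Total | Student t power | Welch t power | Normal approximation |
|---|---|---|---|---|
| 16 | 32 | 0.798 | 0.792 | 0.824 |
| 17 | 34 | 0.823 | 0.817 | 0.846 |
| 20 | 40 | 0.882 | 0.878 | 0.898 |

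By t test, 17 per arm (**34 in total**) is the smallest size with power of at least 0.80. The stated 40 is 6 to 8 patients above the requirement, and its power is 8 to 10 percentage points above the stated 0.8. Rounding does not explain this.

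**Possible roles for the 60%**
- Inflation by 1/0.6, two-sided: 32/0.6 = 53.3, so 54; 34/0.6 = 56.7, so 57. Not 40.
- Effect diluted to 60%, SDs unchanged: difference 0.6 × 1,064 = 638.4; n = 15.05/0.36 = 41.8, so 42 per arm (84 in total). Not 40.
- Inflation by 1/0.6, one-sided: (1.645 + 0.842)² × 2,170,269 / 1,064² = 11.85, so 12 per arm (24 in total); 24/0.6 = 40. This matches, but needs a one-sided α that is not stated.

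**Routes to 40 without the 60%**
- 32/(1 − 0.20) = 40, or 34/(1 − 0.15) = 40. Both need an attrition allowance that the section does not state.

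**What 40 patients provide under different assumptions (two-sided)**
- Complete data, stated effect: about 0.88 by t test.
- 16 per arm with week-8 data (20% lost): about 0.79 (Welch) to 0.80 (Student).
- Assumption only, mean effect diluted to 60% with SDs unchanged: about 0.47 (Welch) at 20 per arm. If the treated arm is instead modelled as a mixture of 60% with the full effect and 40% at baseline values, its SD is √(0.6 × 1,275² + 0.4 × 738² + 0.6 × 0.4 × 1,064²) ≈ 1,210 and power is about 0.50.
- One-sided route, counting only the 12 per arm taken to carry the effect: 0.66 (Welch), 0.67 (Student) or 0.71 (normal approximation).

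**The case against.** The strongest reply is that 40 can be reached from the printed numbers. Sidedness is not stated, and a one-sided requirement of 24 divided by 0.6 is exactly 40, using every figure in the section. It would therefore be too strong to say that the 60% can have no role, or that 40 cannot follow from the inputs. That part of the reply stands. It remains a guess, though. One-sided testing appears nowhere in the article, the P<0.05 rule is unqualified, and the Discussion expects some cytokines to fall and others (IL-4 and IL-10) to rise. Dividing by 0.6 would also make sense only if the remaining 40% were set aside, and neither the eligibility criteria nor the statistical methods do that.

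A second reply is that the surplus over 32 to 34 is an ordinary margin for losses, detailed in a fuller document. This is plausible, since exclusions during follow-up are foreseen. But the section calls 40 the minimum and links it to the 60%, not to attrition.

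A third reply is that the discrepancy does no harm: on the plain two-sided reading 40 more than meets a target of 0.80. This is correct and limits the severity.

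A reader might also infer from the 60% that the trial has only about 47% power. The documents do not support this. Nowhere do they say that only 60% of patients can respond, and the figure moves to about 0.50 with a different assumption about the variance.

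**Conclusion.** The concern holds as a failure to reproduce. For a two-sided, 1:1 comparison of two means on the stated IFNγ values, the requirement is 32 (normal approximation) or 34 (t test), not 40, and 20 per arm gives power of about 0.88 (0.90 by normal approximation), not 0.80. The 60% is not an input to that calculation and its use is unexplained.

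The conclusion rests on two assumptions: that α is two-sided, and that the printed means and SDs are meant as the two group values for the planned test. It does not show that the trial is underpowered or the wrong size, because on this reading the error is on the safe side. Nor does it establish what the 60% did; only the authors can say. This should be fixed, as a correction to the reported justification.

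**What to change.** Rewrite the sample size paragraph so that it:
- states that α = 5% is two-sided;
- gives the requirement on the stated means and SDs as 16 per arm (32) by normal approximation, or 17 per arm (34) by t test, for power 0.8;
- states that 20 per arm will be randomised, giving power of about 0.88 with complete data and about 0.79 if 16 per arm have week-8 data, and says whether the surplus is an attrition allowance;
- either removes the 60% clause or states how it was used, with the resulting two-sided power. If the authors meant that the mean effect is diluted to 60%, that assumption and its power (about 0.47 with SDs unchanged) should be written down.

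The authors should confirm the role of the 60% before deleting it, since it may be the real source of the 40. The cost is one paragraph of text. Enrolment, allocation and analysis do not change.

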The fatty acid composition of inflammatory cells can be modified by increasing the intake of marine *n*-3 fatty acids, which leads to a higher content of eicosapentaenoic acid (EPA) and docosahexaenoic acid (DHA). A number of cell culture studies have reported that both EPA and DHA decrease the activation of the transcription factor nuclear factor κB (NFκB) in response to inflammatory stimuli, such as lipopolysaccharide and inflammatory cytokines [22]. Omega-3 PUFAs reduce arachidonic acid content in cell membranes, resulting in the synthesis of eicosanoids that have weaker inflammatory properties than the eicosanoids derived from omega-6 PUFAs [23].

Omega-3 supplementation is safe and well tolerated in infectious disease as demonstrated in HIV-infected patients treated with antiretroviral therapy [24,25], and on host resistance to infection from *Plasmodium berghei* or *Plasmodium falciparum*, the causative agents of malaria [26], which like Chagas disease is a parasitic infection.

Several studies involving supplementation of the diet with marine *n*-3 PUFAs in healthy human volunteers have demonstrated decreased production of tumor necrosis factor α (TNFα), interleukin 1β (IL-1β), IL-2, and IL-6 [22,23,27]. Omega-3 PUFA supplementation for 8 weeks has been associated with an increase of peripheral mononuclear cells with high concentrations of EPA and DHA, which have an immunomodulating effect [28]. In healthy adults, fish oil supplementation at 5 mL/day for 8 weeks reduced the production of IL-6 but did not change the production of IL-10, TNFα, or IFNγ [29]. Long-chain omega-3 PUFA (EPA and DHA) plasma levels are inversely associated with the risk of sudden death [30] and may reduce the risk of ischemic heart disease [31]. EPA and DHA are also involved in the reduction of plasma very-low-density lipoprotein cholesterol (VLDL-c) and triglycerides [32].

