### Statistical methods

The EpiData [53] and Statistical Package for Social Sciences [54] software will be used for data entry and analysis, respectively. For categorical data, we will use Pearson’s χ^2^ or Fisher’s exact test to verify the association between variables in the two groups (omega-3 and placebo). Statistical analysis will be performed by descriptive analysis, with numerical variables expressed as the mean and standard deviation (SD) or median and interquartile range. The Kolmogorov-Smirnov test will be used to test the normality of the sample distribution. The Student t test will be used in cases with a normal distribution to compare means between the two groups. The Wilcoxon test will be used in cases with a non-normal distribution. *P* values <0.05 will indicate a significant association in all of the statistical tests used.

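### The sample size rests on a before-after fall in IFNγ under supplementation, while the trial tests omega-3 against placebo; the 0.8 power needs a nearly unchanged placebo arm with the baseline SD, and neither assumption is stated

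*Protocol article*

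**What the plan says.** Under the heading Minimum sample size estimation, the protocol article gives a total of 40: "The minimum estimated sample size is 40 patients according to previous data, considering a prevalence of 60% of inadequate PUFA intake". The numerical inputs follow: "The following parameters were considered: baseline IFNγ = 3,986 ± 738 pg/mL, IFNγ after" n-3 supplementation, and then "PUFA supplementation = 2,922 ± 1,275 pg/mL [56], power = 0.8, and α = 5" percent. Both means therefore describe IFNγ around supplementation, one before and one after. No mean, SD or expected change is given for patients on corn oil.

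The design is a 1:1 placebo-controlled parallel trial. Under Randomization and concealment, "patients will be randomly assigned to 1 of 2 groups of 20 patients each: intervention group or control group". Under Statistical methods, "The Student t test will be used in cases with a normal distribution to compare means between the two groups", with a Wilcoxon test if the data are not normal. Under Procedures, follow-up, and data collection, cytokines are measured before the intervention and at week 8.

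**The concern.** A before-after change in supplemented patients contains everything that happens over the period: the treatment effect, drift, regression to the mean and any placebo response. A between-arm comparison removes whatever the two arms share. The two contrasts agree only if the placebo arm stays where it started.

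The spread raises a second question. The two-sample calculation needs a week-8 SD for placebo. The only candidate for an unsupplemented group is the baseline SD of 738, yet the only post-treatment SD in the article is much larger, 1,275.

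At stake is the meaning of the 0.8. If part of the 1,064 pg/mL is shared by both arms, or the placebo arm is more variable than at baseline, the trial may be well short of that power for IFNγ, the one cytokine on which it is sized.

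**Working it through.** **Inputs** (Minimum sample size estimation, unless noted): means 3,986 and 2,922 pg/mL; SDs 738 and 1,275; power 0.8; α 5%, taken as two-sided because sidedness is not stated; 20 per arm (Randomization and concealment). I take the test to be on week-8 values.

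**Effect.** 3,986 − 2,922 = 1,064 pg/mL, or 1,064/3,986 = 26.7% of baseline. Root-mean-square SD = √((738² + 1,275²)/2) = 1,041.7, so the standardised effect is 1,064/1,041.7 = 1.02.

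**Can 40 be reproduced?** Two independent means, normal approximation:

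n per arm = (738² + 1,275²)(1.960 + 0.842)²/1,064² = 2,170,269 × 7.849/1,132,096 = 15.05, so 16 per arm (32 total).

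By Welch t, 16 per arm gives 0.79 and 17 gives 0.82, so 17 per arm (34 total). Other settings do not give 40 either (normal approximation):
- one-sided 5%: 24 total
- two-sided with 90% power: 42 total
- SD 1,275 in both arms: 46 total
- a paired before-after test: 6 to 16 patients for correlations from 0.75 down to 0

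A 20% loss allowance does give 40 (16/0.8 = 20 per arm), but none is stated.

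**Power at 20 per arm, SDs 738 (placebo) and 1,275 (omega-3).** Standard error = √((738² + 1,275²)/20) = 329.4; Welch df = 30.4. Power comes from the noncentral t with noncentrality = difference/329.4.

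| Between-arm share of 1,064 | Implied placebo fall | Difference | Noncentrality | Power |
|---|---|---|---|---|
| 100% | 0 | 1,064 | 3.23 | 0.88 |
| 90% | 106 | 958 | 2.91 | 0.80 |
| 75% | 266 | 798 | 2.42 | 0.65 |
| 50% | 532 | 532 | 1.61 | 0.35 |

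Power is exactly 0.80 at a difference of 953 pg/mL. The tolerable placebo fall is therefore 1,064 − 953 = 111 pg/mL, or 111/1,064 = 10% of the effect.

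**If the placebo SD is also 1,275 (assumption).** Standard error = 1,275 × √(2/20) = 403.2; noncentrality = 1,064/403.2 = 2.64; df 38; power 0.73. By the t test, 23 per arm gives 0.79 and 24 gives 0.81, so 24 per arm would be needed. For 75% and 50% of the effect at 20 per arm, power is 0.49 and 0.25.

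**If only 16 per arm are evaluable** (20 less an assumed 20%). With SDs 738 and 1,275 and no placebo change, power is 0.79. With a placebo fall of 10% of the effect it is 0.70.

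**Effect of baseline adjustment** (correlation ρ assumed, SD 1,275 in both arms, 20 per arm). Residual SD = 1,275 × √(1 − ρ²).
- ρ = 0.5: 1,104; noncentrality 1,064/(1,104 × √0.1) = 3.05; power about 0.84.
- ρ = 0.7: 911; noncentrality 3.70; power about 0.95.

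**The case against.** A reader might infer that the stated power holds only if placebo does not change at all. The figures do not support that. At 20 evaluable per arm there is a margin: power is 0.88 with no placebo change and stays at 0.80 up to a fall of about 111 pg/mL, while a placebo rise would increase it. The strict reading is close to true only if about 16 per arm are evaluable.

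A reader might also take 73% as the trial's true power. It is one end of a range. The SD of 1,275 is documented only after supplementation and says nothing direct about patients on corn oil.

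The Background cites an 8-week fish-oil study that "did not change the production of IL-10, TNFα, or IFNγ". That is a caution about the assumed 27% fall and does not contradict it: the participants were healthy adults on 5 mL/day, and the outcome was cytokine production, whereas this trial measures serum cytokines in patients with cardiomyopathy.

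Three further points are fair. The article does not say how the two means entered the calculation. Whether the cited source had a control arm cannot be checked from the article. And a condensed article may leave out a loss allowance given in a fuller protocol, so the gap between 32–34 and 40 is not by itself proof of an error.

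What survives is what the article does state: the inputs form a before-after contrast, the test is between groups, and nothing bridges the two.

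**Conclusion.** The concern holds in this limited form. The 0.8 power is not shown to belong to the comparison that will be tested. It carries over only if placebo IFNγ falls by no more than about 10% of the assumed effect, the placebo SD stays at 738, and all 40 patients are evaluable.

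Over the ranges considered, unadjusted power at 20 per arm for the full effect runs from 0.88 (placebo SD 738) to 0.73 (placebo SD 1,275). For half the effect it runs from 0.35 to 0.25. If the step from 32 to 40 was a loss allowance, and that loss occurs, power is about 0.79 even with no placebo change. The margin above 0.8 would then be gone.

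These figures rest on a two-sided 5% test of approximately normal week-8 values. The placebo changes, the placebo SD of 1,275 and the loss rate are my assumptions, since the article gives none. The defect lies in the justification of the sample size; it does not show that 40 patients are too few, because baseline adjustment could restore the power.

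**What to change.** 1. Restate the sample-size basis as a between-arm difference in week-8 IFNγ. Give the assumed placebo mean and SD, the sidedness of α, and any loss allowance that takes 32–34 patients to 40.
2. Report power at 20 per arm as a range: 100%, 75% and 50% of 1,064 pg/mL, crossed with a placebo SD of 738 and 1,275. Do not replace 0.8 with a single 73%.
3. Make the week-8 comparison baseline-adjusted (analysis of covariance), and show its power under stated correlations such as 0.5 and 0.7.

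The cost is rewording and one change of analysis model, to be fixed before unblinding. Baseline cytokines are already collected, so no extra patients, visits or assays are needed. The unadjusted power statement may look less favourable for a smaller effect or a larger placebo SD; adjustment may recover much of that if the baseline correlation is moderate or better.

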### Ethical issues

The study was approved by the Research Ethics committee of the Evandro Chagas Clinical Research Institute (IPEC/FIOCRUZ), registration number CAAE-0037.0.009.000-10 [58]. It is registered at ClinicalTrials.gov, number NCT01863576. All study supplies and data collected will be used exclusively in this study, and its results will be made public, whether they are favorable or not.

## Discussion

Omega-3 PUFA intake is associated with beneficial health effects. Omega-3 PUFAs are helpful in the prevention and treatment of pathologies such as inflammatory diseases, hypertension, hypertriglyceridemia, metabolic syndrome, and heart diseases. An Italian study of heart failure patients showed a reduction in mortality and hospital admissions due to cardiovascular events, suggesting beneficial effects of omega-3 PUFAs on the progression of heart disease [33].

Omega-3 administration is effective at treating hypertriglyceridemia. According to clinical trials, supplementation with 2 to 4 g of EPA/DHA per day may reduce triglyceride levels by 25% to 30% [59] by decreasing the liver synthesis of VLDL-c [34]. Omega-3 supplementation for chronic chagasic cardiomyopathy may be similar to other cardiomyopathies and promote reductions in triglyceride and VLDL-c levels.

Omega-3 has beneficial effects against heart cachexia after 18 weeks of supplementation [43]. Women with polycystic ovarian syndrome and BMI between 25 and 40 kg/m^2^, however, exhibited no significant changes in BMI after supplementation for 8 weeks [60]. The period of treatment in this study may not be long enough to observe significant anthropometric changes after omega-3 administration with no other associated instruction or intervention.

The action of omega-3 PUFAs is most likely related to their anti-inflammatory effects, which are not yet completely understood; however, it is known that omega-3 PUFA supplementation reduces arachidonic acid content in cell membranes, resulting in the synthesis of eicosanoids that are less inflammatory than the ones derived from omega-6 PUFAs [23]. Omega-3 PUFAs can also decrease activation of NFκB in response to inflammatory stimuli, such as lipopolysaccharide and inflammatory cytokines [22]. A meta-analysis of the effects of fish oil supplementation on the inflammatory markers of patients with chronic heart failure showed that circulating TNFα, IL-1, and IL-6 (proinflammatory cytokines) decreased after a supplementation period of 3 to 12 months with an EPA and DHA dose of 600 to 5,540 mg/day. These data suggest that supplementation with higher doses of omega-3 PUFAs or longer follow-up times are associated with more substantially decreased cytokines [61], which could benefit CCC patients.

A clinical trial evaluated 3-month omega-3 PUFA supplementation in patients with heart failure. Patients were divided into three groups: placebo, 1 g/day omega-3 PUFAs, and 4 g/day omega-3 PUFAs. Only the 4 g/day group had an improvement in ventricular function with an increase in the ejection fraction and endothelial function and a reduction in IL-6 [36]. We will use 3 g/day omega-3 PUFAs in our study based on recent results suggesting higher efficacy when compared to the usual 1 g dose, in addition to the fact that 3 g/day is considered safe by the FDA [51]. According to a recent American College of Cardiology and American Heart Association (ACC/AHA) Heart Failure Guideline, omega-3 supplementation is reasonable to use as adjunctive therapy in heart failure patients (Class of Recommendation IIa, Level of Evidence B ) [62].

The worse prognosis and progression of CCC are related to increased immune response with the production of proinflammatory cytokines and the inhibition of anti-inflammatory cytokines, which also occur in other cardiomyopathies [63,64]. In Chagas disease, heart tissue is an important target of *T. cruzi* infection, and substantial amounts of proinflammatory cytokines, chemokines, and enzymes, including inducible nitric oxide synthase and metalloproteinases, are produced, resulting in inflammation and cardiac remodeling in response to parasite infection [65]. Higher levels of IFNγ and TNFα are associated with lower levels of IL-4 and IL-10, in both cardiac and more severe forms of Chagas disease, and high levels of IL-10 or moderate levels of IFNγ are associated with the indeterminate form [15,66]. Omega-3 and omega-6 PUFA intake may lead to an increase in IL-10 production, as shown in an experimental study in Wistar rats supplemented with ethyl-eicosapentaenoic acid and ethyl-γ-linolenic acid compared to a group supplemented with palm oil [67]. Thus, omega-3 PUFA supplementation in CCC patients may lead to increased IL-4 and IL-10, reducing the inflammatory effect on heart tissue.

Omega-3 PUFA supplementation, due to its anti-inflammatory effects, is expected to decrease the serum levels of proinflammatory cytokines, which are associated with the proliferation of parasites and the fibrotic process characteristic of Chagas myocarditis. We thus suppose that the benefits to CCC patients with regard to the immunological profile could translate into a less severe progression of cardiomyopathy, with subsequent reduction in morbidity, in addition to secondary gains in the lipid profile.

